### Inclusion and exclusion criteria

All adult patients (≥18 years) undergoing single-shot regional anesthesia of the upper limb, lower limb, or fascial plane will be considered eligible for inclusion after providing informed consent.

Patients will be excluded if they are not able to provide informed consent or if they are receiving multiple regional anesthesia techniques. However patients receiving more than one single-shot regional block during the same operative session may be included if the blocks do not share potential complications or overlapping sensory innervation. For example, a patient undergoing both an interscalene plexus block for shoulder surgery and a femoral nerve block for knee surgery may be included, as the two blocks involve distinct innervation areas and complication profiles. Conversely, patients receiving both a paravertebral block and an erector spinae plane (ESP) block on the same side of the chest would not be eligible, since these techniques share common risks (e.g., pneumothorax) and overlapping innervation, making it impossible to attribute complications to a specific block. However, a patient receiving a paravertebral block on one side of the chest and an ESP block on the opposite side could be included, as no overlap in innervation or complication risk would be expected in this scenario.

### Recruitment

Participants will be recruited from as many centers as possible, subject to approval by their respective ethics committees. The centers initially involved in the steering committee include: Azienda Ospedale–Università di Padova, Padua, Italy; ASST Grande Ospedale Metropolitano Niguarda, Milan, Italy; ASST Papa Giovanni XXIII, Bergamo, Italy; and Humanitas Rozzano, Rozzano (MI), Italy. At the time of submission of this protocol, 43 centers had joined the study. The list of centers participating in the NEURAL study will be continuously updated on the official *ClinicalTrials.gov* record. (the complete list of participating centers is available on *ClinicalTrials.gov*). The list of centers participating in the NEURAL study will be continuously updated on the official *ClinicalTrials.gov* record (NCT07238933; first submitted on 02.10.2025, publicly available since 20.11.2025) as new centers join the study.

### Data collection

Following informed consent, data will be collected using a standardized collection form. Each data entry will be generated by a participating center and recorded on SIAARTI servers through the REDCap® (Research Electronic Data Capture) data management software. REDCap is a secure web-based platform designed to facilitate data capture and management for research studies.

The following data will be registered:

### Intraoperative time

- Demographics: age (years), sex (male/female), BMI (kg/cm^2^).- Medical history: relevant comorbidities (i.e., arterial hypertension, diabetes mellitus, peripheral neuropathy, central neuropathy).- Medication history: with particular attention to anticoagulant and antiplatelet agents, including type and dosage.- Intraoperative data:pre-procedural sedation (i.e., type of drug), and, if sedation was performed, the level of sedation at the time of block execution — assessed using the Richmond Agitation Sedation Scale (RASS) scaletype of regional anesthesiaNeedle used (sharp vs not-sharp and diameter in gauge)use of ultrasound (yes/no, visualization of structures yes/no, in-plane or out-of-plane approach, nerve swelling on injection yes/no)use of a nerve stimulation device (maximum and minimum intensity used)use of a pressure limitertype of local anesthetic used (volume and dose in mg)single local anesthetic drug or mixture of local anesthetic drugsuse of adjuvants (type and dosage in mg or mcg)pain on injection (yes/no)presence (yes/no) of complications, such as hematoma (yes/no) and nerve deficits (yes/no), and their characteristics (sensory – dysesthesia, anesthesia, paresthesia –, or motor deficits in the affected area) at 24 and 48 hours.

As nerve deficits may not be immediately apparent and can be masked by factors such as local edema or limb immobilization [7]. Therefore, sensory and motor deficits will be investigated at 15 and 30 days through a standardized telephone questionnaire aimed at assessing sensory loss, motor impairment, and neuropathic pain (see S2 File). Patients who report the presence of sensory or motor neurological deficits will be referred for management according to the practices of the participating center. For research purposes, they will receive a telephone call every 30 days to monitor the evolution of the deficit until resolution, with a maximum follow-up period of one year.

In summary, the evaluation of complications will require patient contact (either through in-person visits or telephone contact if discharged) at 24 and 48 hours, as well as 15 and 30 days. In the event of nerve complications, the treatment of the lesion will follow the hospital’s local protocol. For the study, follow-up will continue every 30 days until the deficit resolves, or for a maximum of one year from its onset. A timeline is available as Fig 1.

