### Study design and objectives

This protocol has been prepared with the support of the SPIRIT checklist (see S1 File). The NEURAL study, promoted by the Italian Society of Anesthesia, Analgesia and Critical Care (SIAARTI), is a multicenter, prospective observational study designed to investigate the prevalence of complications associated with regional anesthesia of the upper limb, lower limb, and fascial plane blocks.

The primary objective of the NEURAL study is to determine the overall incidence of complications following regional anesthesia, expressed as a composite outcome. This composite outcome will include nerve injury, hematoma, pneumothorax, and LAST, calculated as the total number of complication events divided by the total number of procedures.

The secondary objectives are to determine the incidence of each individual complication (nerve injury, hematoma, pneumothorax, and LAST for each type of regional anesthesia technique. These include upper limb blocks, lower limb blocks, and fascial plane blocks (Table 1), with outcomes calculated as the number of events relative to the total number of procedures performed. In addition, the study seeks to identify risk factors associated with complications following upper limb regional anesthesia, lower limb regional anesthesia, and fascial plane blocks, thereby contributing to a more precise understanding of patient- and procedure-related variables influencing safety in regional anesthesia as described in the relevant paragraph below..

**Table 1 pone.0348493.t001:** Fascial plane regional anesthesia: The most recent nomenclature of the European Society of Regional Anaesthesia (ESRA) [7] will be used. The following blocks will be considered.

Upper limb blocks	Lower limb blocks	Fascial blocks

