### Definitions

Complications will be defined as follows:

Hematoma: A blood collection at the regional anesthesia site requiring medical and/or surgical intervention.Pneumothorax: The presence of an air crescent consistent with pneumothorax on the same side as the regional anesthesia, confirmed by ultrasound, chest X-ray, or chest CT scan.LAST: Any electrocardiographic, hemodynamic, and/or neurological alteration occurring after regional anesthesia, attributable to systemic absorption of local anesthetic and requiring treatment (e.g., lipid emulsion administration).Nerve injury: The onset of dysesthesia, anesthesia, or prolonged motor deficit not explained by the pharmacokinetics of the anesthetic used, within the distribution area consistent with the performed block.

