### Strengths and limitations

A key strength of the NEURAL study lies in its multicenter, prospective, and observational design, coordinated under the auspices of SIAARTI. The inclusion of multiple tertiary centers across Italy ensures broad representation of clinical practice, patient demographics, and procedural variability, thereby enhancing the generalizability of results.

The study’s standardized definitions of complications and structured follow-up at 24 and 48 hours, as well as at 15 and 30 days—with extended follow-up up to one year for nerve injury—will enable accurate detection of both early and delayed complications. The detailed recording of procedural variables (e.g., ultrasound guidance, injection pressure, adjuvants used) and patient characteristics (e.g., comorbidities, anticoagulant use) allows for in-depth risk factor analysis using multivariable modeling.

However, the study also has inherent limitations. As an observational protocol, it cannot establish causal relationships between regional anesthesia and complications. Additionally, the identification of rare events may still be constrained by the sample size, despite careful power calculation. Potential variability in operator experience and institutional practices may introduce confounding, though standardized definitions and training across centers are intended to minimize this effect.

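### The day-15 and day-30 contacts are described as neurological only, so late hematoma and pneumothorax have no described route into a primary composite that has no stated time window

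*Protocol article*

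**What the plan says.** Study design and objectives sets the primary endpoint in one sentence: "This composite outcome will include nerve injury, hematoma, pneumothorax, and LAST, calculated as the total number of complication events divided by the total number of". The denominator is procedures. No time window is attached. The secondary objectives ask for the incidence of each component by type of block.

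Intraoperative time (under Data collection) lists what is recorded at 24 and 48 hours: "presence (yes/no) of complications, such as hematoma (yes/no) and nerve deficits (yes/no), and their characteristics". For days 15 and 30 it describes a "standardized telephone questionnaire aimed at assessing sensory loss, motor impairment, and neuropathic pain". The reason given is that nerve deficits can be masked early on. The summary in the same section is broader: "the evaluation of complications will require patient contact (either through in-person visits or telephone contact if discharged) at 24 and 48 hours" and again at 15 and 30 days. For nerve complications, "follow-up will continue every 30 days until the deficit resolves, or for a maximum of one year from its onset".

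Definitions describes nerve injury as "The onset of dysesthesia, anesthesia, or prolonged motor deficit not explained by the pharmacokinetics of the anesthetic used", within the area of the block. Hematoma qualifies by needing intervention, pneumothorax by imaging, and LAST by needing treatment.

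Strengths and limitations says that the definitions and follow-up schedule "will enable accurate detection of both early and delayed complications".

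**The concern.** The general statements promise follow-up of complications as a whole, while the only content described for the two late contacts concerns nerves. Followed as written, nerve injury is actively sought to day 30. Nobody is described as asking about bleeding at the block site or about a pneumothorax after 48 hours. With no window for the composite, a reader cannot tell whether such a late event should count, or how it would become known.

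The primary result is an absolute incidence in a single cohort. No comparison between arms can cancel the under-counting, and an analysis plan cannot recover answers to questions that were never put. The component incidences would also be read side by side although they rest on different intensities of search.

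**Working it through.** **1. The four components side by side**

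| Component | What makes it an event (Definitions) | 24 and 48 h | Days 15 and 30 |
|---|---|---|---|
| Nerve injury | Onset of a listed deficit, not pharmacokinetic, in the block's area | Named | Content of the questionnaire |
| Hematoma | Needs medical or surgical intervention | Named | No question described |
| Pneumothorax | Confirmed by imaging, same side | Not named, but the list is illustrative | No question described |
| LAST | Attributable to absorption, needs treatment | Not named, but the list is illustrative | No question described |

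Intervention for a hematoma and imaging of a pneumothorax can each first happen after discharge and after 48 hours, so those two components carry the gap. For LAST the late gap should matter little if it is an early event, which is an assumption here.

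**2. What one missed event is worth**

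Inputs from Sample size calculation: incidence 0.005 and minimum N = 3,396. I take one procedure per subject.

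- Expected events: 3,396 × 0.005 = 16.98, about 17.
- One event as a share of the count: 1/16.98 = 5.9%.
- One event as incidence: 1/3,396 = 0.029 percentage points.

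The plan's 3,396 does not reproduce from its stated total width of 0.003. Agresti-Coull uses ñ = n + z², p̃ = (np + z²/2)/ñ and width = 2z√(p̃(1 − p̃)/ñ). At p = 0.005 and 95% confidence:

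- width 0.003 needs n = 8,853;
- width 0.005 needs n = 3,395, which matches the plan's figure to within one subject.

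That is a separate matter and neither supports nor weakens this point. It does affect the weight of a single event: at 8,853 subjects, 8,853 × 0.005 = 44.3 events are expected and one event is 1/44.3 = 2.3% of them. The abstract expects enrollment above 3,396, so 6% applies at the minimum size.

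**3. Illustration of the total effect (assumed inputs)**

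Let s be the share of true events that are hematoma or pneumothorax, and m the fraction of those missed. The documents give neither. Observed incidence = 0.005 × (1 − s·m), and the proportional loss s·m does not depend on N.

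| s | m | s·m | Observed incidence | Events at N = 3,396 |
|---|---|---|---|---|
| 0.2 | 0.1 | 2% | 0.49% | 16.6 |
| 0.4 | 0.3 | 12% | 0.44% | 14.9 |
| 0.6 | 0.5 | 30% | 0.35% | 11.9 |

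The range runs from negligible to material. It shows only that the answer depends on quantities the plan does not give.

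**4. Symptoms recorded against symptoms defined**

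The definition of nerve injury names dysesthesia, anesthesia and prolonged motor deficit. The 24/48-hour record also includes paresthesia, and the late questionnaire includes neuropathic pain. The article does not say whether either of these alone makes an event. The word prolonged carries no duration. Monthly calls run for up to a year, but no objective uses persistence.

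**The case against.** The best reply is that this is a condensed article. The collection form, the telephone questionnaire (S2), the full protocol (S3) and the timeline figure are not shown. The questionnaire is described by its aim, which need not exhaust its content, and the summary sentence refers to complications at all four contacts. The late neurological focus has a stated reason. Hematoma, pneumothorax and LAST as defined all involve medical attention, so they depend less on a symptom interview. These arguments limit the certainty of the point but do not remove it. The article describes no late question and no record review for these components, and its own statements about late contacts do not agree.

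Three stronger readings are tempting, and the documents do not support them.

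- A reader might infer that LAST and pneumothorax go unrecorded at 24 and 48 hours. The field list is introduced as examples, so absence from it proves nothing.
- A reader might infer that any deficit seen at 24 hours counts without restriction and that false positives then dominate. The 24-hour mark is a contact time, not a qualifying time. The definition excludes pharmacokinetic explanations and requires the block's distribution. No misclassification rate is given, so dominance cannot be shown.
- A reader might want only persistent deficits in the primary count. That would change the endpoint from onset to persistence. It is a debatable trade-off, not the correction of an error.

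Standardized definitions and training, and the center-level random intercepts, address variation between centers. They do not supply a question that is not asked.

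**Conclusion.** The point holds in a limited form. The composite has no stated window. The only described content at days 15 and 30 is neurological, and this conflicts with the general wording on evaluating complications and on detecting delayed ones. The likely direction is under-counting of late hematoma and pneumothorax, both in the composite and in their own incidences. At the plan's minimum size each missed event is about 6% of roughly 17, or 0.03 percentage points. The number missed is unknown, so no net bias can be stated. The conclusion assumes that the unshown questionnaire and form contain no further late questions. If they do, only the window and the wording need correcting.

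**What to change.** 1. Add two questions to the existing day-15 and day-30 calls: whether bleeding at the block site was treated, and whether a pneumothorax was diagnosed since the block. Record the date.
2. State one 30-day window for the composite and for its components.
3. Reconcile the description of the late questionnaire with the summary in Intraoperative time and with the claim in Strengths and limitations.
4. Keep the primary nerve-injury definition based on onset, and state whether isolated paresthesia or neuropathic pain qualifies.
5. Report separately the deficits that are transient, that persist at 30 days and that persist at one year, from the calls already planned.

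The cost is slightly longer calls, some form and wording changes, and recall-based reports that need checking against records. The article says the study had not started at submission. If recruitment has since begun, the date of the change should be recorded, because patients called before it will lack these answers.

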**Fig 1 pone.0348493.g001:**
[figure not shown]
Participant timeline: Schedule of enrollment, intervention, and assessments.

### Statistical analysis

Data for each continuous variable will be analyzed to assess the normality of distribution using the Shapiro-Wilk test. Continuous variables with normal distributions will be reported as mean (standard deviation); those with non-normal distributions will be reported as median and interquartile range. Analysis of normally and non-normally distributed data will be performed using the two-tailed Student’s t-test and the Mann-Whitney U test, respectively.

If the proportion of missing data exceeds 5% for key variables, multiple imputation by chained equations will be performed under the assumption of missing at random. Imputation models will include all variables used in the primary analyses, including outcomes and relevant predictors. Sensitivity analyses will be conducted to compare complete-case analyses with imputed datasets. In addition, if differential loss to follow-up is observed, inverse probability weighting methods may be applied to assess the robustness of the findings. The amount of missing data and the methods used to address it will be transparently reported according to STROBE recommendations.

Results for categorical variables will be reported as numbers (percentages) and compared between groups using the chi-squared test or Fisher’s exact test, as appropriate.

To determine the strength and direction of association between two variables, the Bravais-Pearson correlation test will be used for variables with a normal distribution, and the Spearman rank correlation test for variables not meeting normal distribution assumptions.

To determine the relationships between the dependent categorical variable (e.g., complications) and one or more independent categorical variables (i.e., complication predictors), logistic regression will be performed to calculate odds ratios (OR) with 95% confidence intervals (CI). Given the anticipated low incidence of complications, rare-event bias may affect conventional maximum likelihood estimation. Therefore, penalized likelihood approaches—such as Firth’s bias-reduced logistic regression—will be used when appropriate to improve the stability and validity of parameter estimates. In cases of extremely sparse data, exact logistic regression methods may also be considered. Model adequacy will be assessed using goodness-of-fit statistics and calibration plots. The presence of multicollinearity will be assessed using variance inflation factors.

Given the exploratory nature of this large observational study and the evaluation of multiple block types, predictors, and secondary outcomes, we recognize the potential risk of false-positive findings due to multiple comparisons. The secondary outcomes and subgroup analyses, effect sizes and 95% confidence intervals will be emphasized rather than sole reliance on p-values. Where appropriate, false discovery rate control using the Benjamini-Hochberg procedure may be applied to secondary analyses to reduce the risk of Type I error inflation. All secondary analyses will be interpreted cautiously and considered hypothesis-generating.

#### Accounting for center-level clustering.

Given the multicenter design of the NEURAL study, patients are clustered within participating institutions, and outcomes may be correlated due to shared clinical practices, operator expertise, equipment, or local protocols. To account for this hierarchical structure, multilevel (mixed-effects) regression models will be used for the primary and secondary analyses. Specifically, random-intercept logistic regression models will be applied to account for between-center variability when estimating associations between predictors and complications. The intraclass correlation coefficient (ICC) will be calculated to quantify the degree of clustering. As a sensitivity analysis, generalized estimating equations (GEE) with robust standard errors will also be considered.

All statistical analyses will be performed using R software. P-values < 0.05 will be considered indicative of statistical significance.

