### Sample size calculation

This is an observational study aimed at investigating very rare complications, the incidence of which is difficult to estimate. Literature reports an incidence ranging from 0 to 2.8%, depending on the study and cohort considered [8].

The sample size estimation was performed using an approach based on the precision of the proportion estimate, defined as the total width of the confidence interval. For this purpose, the Agresti-Coull Wilson method was applied [9].

Starting from a cumulative incidence of 0.005 (0.5%) [10], with a 95% confidence level and aiming for a confidence interval width of 0.003, a minimum of 3,396 subjects must be enrolled. The estimation was conducted using the {presize} package of R software, version 4.3.3 (2024-02-29 ucrt).

When the study was initially planned, we anticipated enrolling at least 10 centers in the NEURAL study, with an expected average recruitment of approximately 350 patients per center over two years, making the achievement of the planned sample size a realistic goal.

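### The primary analysis is ambiguous between a crude incidence and a mixed model, and the precision calculation makes no allowance for the within-center correlation that the plan considers possible

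*Protocol article*

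**What the plan says.** **Primary outcome.** Under Study design and objectives, "The primary objective of the NEURAL study is to determine the overall incidence of complications following regional anesthesia". It is a composite, computed as the count of complication events over the count of procedures. Risk factors are a secondary objective.

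**Clustering.** The section on center-level clustering says that "patients are clustered within participating institutions, and outcomes may be correlated due to shared clinical practices" and other local factors. It then says that "multilevel (mixed-effects) regression models will be used for the primary and secondary analyses". The next sentence applies random-intercept logistic models to the estimation of predictor-complication associations. The ICC is to be estimated from the data. GEE is to be considered as a sensitivity analysis.

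**Sample size.** The approach is the precision of one proportion, with precision "defined as the total width of the confidence interval". The section states that "the Agresti-Coull Wilson method was applied". The inputs are an incidence of 0.005 and the target, "with a 95% confidence level and aiming for a confidence interval width of 0.003". The result is at least 3,396 subjects. No ICC, design effect or number of centers enters the calculation; centers appear only in a remark on feasibility.

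**The concern.** There are two linked difficulties.

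1. **Which quantity is the headline?** Events over procedures is a population-level proportion. The inverse-logit of the intercept in a random-intercept logistic model is the risk in a center whose random effect is zero. For a rare outcome it lies below the population proportion, and the gap grows with the between-center variance. The two sections do not say how, or whether, the model feeds the primary estimate. A downward shift would be awkward here, because the Introduction hypothesizes that true incidence is higher than registry data suggest.

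2. **How wide is its interval?** If outcomes are correlated within centers, 3,396 patients carry less information than 3,396 independent ones. The planned precision does not allow for this, and if the mixed model serves only risk factors, the article states no center-adjusted interval for the primary result.

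**Working it through.** **Inputs from the protocol.** Incidence p = 0.005, 95% confidence, total width 0.003, n = 3,396 (Sample size calculation); 43 centers joined (Recruitment).

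**Assumed, because the protocol gives none.** Between-center variance on the logit scale of 0.25, 0.5 or 1.0; equal center sizes.

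**Step 1: the plan's own figure.** The Agresti-Coull width is 2z√[p̃(1−p̃)/ñ], with ñ = n + z², p̃ = (np + z²/2)/ñ and z = 1.96.

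- At n = 3,396: ñ = 3,399.8, p̃ = (16.98 + 1.92)/3,399.8 = 0.00556, width = 0.0050.
- For a width of 0.003: n = 8,853 (Wilson: 8,676).

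So 3,396 does not follow from a width of 0.003. It matches a width of 0.005 (n = 3,395). This is a separate error that exists before clustering enters. The baseline below is therefore 0.0050.

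**Step 2: intercept risk against overall risk.** Choose b₀ so that expit(b₀ + u), averaged over u ~ N(0, σ²), equals 0.005, by Gauss-Hermite integration. Then expit(b₀) is the risk in a center with u = 0. The probability-scale ICC is Var[expit(b₀ + u)] / [p(1−p)].

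| σ² (assumed) | expit(b₀) | Shortfall against 0.50% | ICC |
|---|---|---|---|
| 0.25 | 0.44% | 12% | 0.0014 |
| 0.5 | 0.39% | 22% | 0.0032 |
| 1.0 | 0.31% | 39% | 0.0081 |

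The approximation p·exp(−σ²/2) gives nearly the same values: 0.44%, 0.39% and 0.30%.

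**Step 3: precision with clustering.** Center size m = 3,396/43 = 79. Design effect DE = 1 + (m − 1) × ICC. Effective n = 3,396/DE, entered in the Step 1 formula (unrounded ICCs used).

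| ICC | DE | Effective n | Agresti-Coull width |
|---|---|---|---|
| 0 | 1.00 | 3,396 | 0.0050 |
| 0.0014 | 1.11 | 3,061 | 0.0053 |
| 0.0032 | 1.25 | 2,722 | 0.0057 |
| 0.0081 | 1.63 | 2,083 | 0.0066 |

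The 46 centers named under Ethical approval would change this little: m = 73.8, DE = 1 + 72.8 × 0.0014 = 1.10 up to 1 + 72.8 × 0.0081 = 1.59.

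**Step 4: how well the center variance can be estimated.** Expected events are 3,396 × 0.005 = 17, or 17/43 = 0.4 per center. A variance or ICC estimated from so few events will be very imprecise.

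**The case against.** **The estimand is already clear.** The objectives section fixes events over procedures. The sentence after the disputed one confines the random-intercept model to associations, and the Statistical analysis section likewise ties logistic regression to predictors and odds ratios. A reader might infer from the disputed sentence that the study will understate its headline incidence. The documents do not support that: nowhere do they say that the intercept will be reported as the incidence, a mixed model can be averaged over centers, and GEE is mentioned. This stands, and it reduces the charge to an ambiguity. It does not remove it, because the only primary objective is an incidence and the sentence names the primary analysis.

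**The plan does not assert correlation.** A reader might take the clustering section as stating that outcomes are correlated. It says only that they may be, and gives no size. This stands; the figures above are conditional on assumed variances.

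**Clustering is not what breaks the stated precision.** A reader might attribute the missed target of 0.003 to clustering. The target already fails under independence (0.0050), and with 43 centers clustering is the smaller part. This stands. A reader might also rely on the 10 centers in the sample-size section, where m = 340 gives DE = 1 + 339 × 0.0014 = 1.5 up to 1 + 339 × 0.0081 = 3.7. The protocol presents that as the initial plan, so it should not carry the argument.

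**The sample-size formula does not prescribe the final interval, and 3,396 is a minimum.** Both are true. The final CI method may be set out in a fuller document, and recruitment above the minimum would narrow the interval. Neither point reconciles the two sections on the primary analysis or adds a clustering term to the precision calculation.

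**Conclusion.** The concern holds as an ambiguity plus an omitted design effect, not as a demonstrated bias. The objectives and clustering sections need reconciling on what the primary analysis is. A headline of 0.44%, 0.39% or 0.31% in place of 0.50% would arise only if the raw intercept were reported as the incidence, and only at the assumed variances.

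The precision calculation assumes independence although the plan allows for within-center correlation. For 43 equal centers and the same variances, clustering adds about 0.0003 to 0.0016 to a width of 0.0050, against a gap of 0.0020 between the stated 0.003 and what 3,396 independent patients deliver. Unequal recruitment across centers would generally raise the design effect; a lower ICC would shrink it toward nothing. The change is worth making because it settles the primary estimate and its error bars at little cost.

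**What to change.** 1. State that the primary incidence is the crude overall proportion, events over procedures, with a 95% CI that allows for center. A bootstrap that resamples centers is one option. It is preferable to dividing n by an estimated design effect, which would rest on a poorly estimated ICC.
2. Reword the clustering section so that the random-intercept model serves risk-factor associations only. If a model-based incidence is also wanted, say that it will be averaged over centers.
3. In the sample-size section, first correct the independent baseline (width and n must agree), then give the expected width over an assumed ICC range, with the number of centers now expected.

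**Cost.** Analysis-plan wording and a somewhat wider stated interval. No new data are needed, and the article reports that the study had not started at submission.
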